### Participants

The pilot study will randomly assign 60 older (60+) Latino participants with minor or subthreshold depression or anxiety to the HOLA intervention (n = 30) or enhanced psychoeducation (n = 30). The sample size is sufficient to provide meaningful data on the feasibility and the other outcome measures of interest. Additionally, this sample size is consistent with other pilot studies of physical activity interventions [38, 39]. Informed consent will be obtained from each participant. For a detailed description of the inclusion/exclusion criteria, see Table 1.

**Table 1 Tab1:** Inclusion/exclusion criteria

Inclusion criteria	Exclusion criteria
• Self-identify as Latino; • Age 60+; • Have minor depression as defined by a primary DSM-IV Axis I diagnosis of minor depressive disorder or subthreshold depression defined as a score ≥ 3 on the Patient Health Questionnaire (PHQ-2), OR subthreshold anxiety as defined as a score ≥ 3 on the Generalized Anxiety Disorder-2 scale (GAD-2); • Absent of episodes of major depression and anxiety disorders for past 12 months; • Volunteer informed consent; • Have medical clearance for participation in an exercise program by a physician, physician’s assistant, or nurse practitioner; • Agree not to use antidepressant medication (since these subjects could have a partially treated episode of major depression or anxiety and thus would be inappropriate for a prevention trial); • Expect to stay in Miami for the next 12 months	• Currently residing in a nursing or group home; • Have a terminal physical illness expected to result in their death within one year; • Have a diagnosis of dementia, comorbid diagnosis of dementia, or significant cognitive impairment; • Presence of any Axis I psychiatric disorder or substance abuse during preceding 12 months; • History of psychiatric disorders other than non-psychotic unipolar major depression or anxiety disorder; • High suicide risk; intent or plan to attempt suicide in the near future; • Taking cognitive enhancing medication or psychotropic medications (e.g., antidepressants); • Unable to complete 10-meter walk test in less than 23 seconds average; • Heart rate exceeds 170 beats per minute OR systolic blood pressure exceeds 180 during 10-meter walk test; • Chest or leg pain, dyspnea, dizziness, feeling faint, or other significant symptoms while completing 10-meter walk test; • Have contraindications to exercise outlined in the American College of Sports Medicine standards.

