#### Intervention description: content and structure of HOLA

The first component of HOLA is a social and physical activation session. Prior to beginning the group exercise phase, each participant will meet individually with a CHW for the physical and social activation session. This session will last 30 minutes. The purpose of this session is to (a) educate potential participants about the goals of the intervention; (b) motivate participants to engage in physical activity; (c) increase participants’ social activities; (d) identify potential obstacles that may interfere with meeting the demands of the intervention; and (e) brainstorm ways to overcome these obstacles. Participants will meet individually with the CHW for 30 minutes after week 8 to discuss progress of physical and social activity goals.

The second component is a moderately intense, group walk, led by a CHW for 45 minutes, three times a week, for 16 weeks. Moderate intensity is defined as a rating between 11 and 13 on the Borg Scale of Perceived Exertion [41]. Walks will be conducted with a group of six participants. Each walk will begin with 10 minutes of stretching and warm up. Then, participants will walk for 30 minutes. The walk will conclude with 5 minutes of stretching and cool down. Blumenthal and colleagues [27] showed that this intensity and amount of physical exercise is associated with greater remission of major depression in older adults. It is hypothesized that this amount and frequency will also be effective in the prevention of major depression and anxiety disorders in older Latinos with subthreshold symptoms. The groups will be mixed gender and will include bilingual and monolingual Spanish-speaking participants.

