### Measures and analysis

#### Feasibility objective: recruitment, randomization, retention, and acceptability

As a pilot study, the randomized prevention trial will examine feasibility. Consistent with recommendations from biostatistical workgroups funded by NIH [45], this pilot study is not powered to test a hypothesis. Successful recruitment will be defined as meeting 100 % of targeted randomization (n = 60), with 20 % or less of eligible subjects refusing randomization. Randomization will be deemed adequate if the randomization scheme produces equal numbers of participants randomized to each condition. Adequate retention will be defined as 85 % or more of randomized subjects completing the post-intervention assessment. Acceptability is defined as 80 % or more of sessions attended by subjects. Data will also be collected on the proposed outcome measures to be tested in a definitive randomized controlled trial.

Study measures will be administered at baseline, end of intervention, and at 6 and 12 months post intervention. Eligible participants will be paid $25 upon completion of assessments at baseline, the end of the intervention, at 6, and at 12 months post intervention for a total of $100. Trained research assistants (RA) will administer all of the assessments and will be kept blind to randomized study assignment.

After the baseline assessment, participants will be randomly assigned to the HOLA intervention or to the *fotonovela* condition. Randomization will be carried out using an automated program embodying the strategies of permuted block randomization.

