#### Analysis

Univariate analyses will be conducted to determine if randomization yielded equivalent groups by comparing demographics, background factors, key outcome variables and important covariates and potential moderators at baseline using chi-square and *t*-tests. Confidence intervals will be examined for differences between group means for all measures as a means of summarizing these analyses. If systematic differences between the two groups are found, propensity score matching will be used in statistical tests of outcomes. As a preliminary evaluation of the interventions, effect sizes will be calculated to assess for evidence of potential effectiveness. However, we accept that the study will not be powered to provide strong evidence against the null hypothesis. An intent-to-treat analysis will be conducted for the outcomes of interest, comparing the participants who were randomized to HOLA with those in the *fotonovela* condition. These analyses permit the strongest inferences to be drawn regarding the effects of physical activity and enhanced psychoeducation, but as previously discussed they may be underpowered. For a more conservative assessment, an as-treated analysis will be conducted, comparing participants randomized to and completing HOLA to those randomized to the *fotonovela*. These analyses may provide a more sensitive measure of the true effect of HOLA on reducing depression and anxiety symptom severity.

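### The HOLA-completers comparison is labelled more conservative and as-treated, but it breaks randomisation in one arm and favours HOLA if completers have a better prognosis

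*Protocol article*

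**What the plan says.** The Analysis section of the protocol article first plans the comparison as randomised: "An intent-to-treat analysis will be conducted for the outcomes of interest, comparing the participants who were randomized to HOLA with those in the" *fotonovela* condition. It ranks that analysis highest for inference and warns that it may be underpowered.

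It then adds: "For a more conservative assessment, an as-treated analysis will be conducted, comparing participants randomized to and completing HOLA to those randomized to the" *fotonovela*. The next sentence says of this second comparison: "These analyses may provide a more sensitive measure of the true effect of HOLA on reducing depression and anxiety symptom severity".

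The two arms ask very different things of participants. HOLA includes a group walk, "led by a CHW for 45 minutes, three times a week, for 16 weeks" (section on the content and structure of HOLA). Controls receive a booklet and one hour-long group discussion a month later (section on the comparison condition).

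The same Analysis section provides for propensity score matching, but only if the two randomised groups differ systematically at baseline.

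**The concern.** Three things are wrong with how the second comparison is described.

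- **Name.** Nobody is reclassified by the treatment actually received, so it is not an as-treated analysis. HOLA non-completers are dropped and all controls are kept.
- **Direction.** Finishing a 16-week walking programme plausibly depends on health, mood and motivation, which may also predict symptom outcomes. Filtering one arm on such behaviour and leaving the other unfiltered does not make an estimate cautious.
- **Consistency.** The text presents the comparison as more cautious than ITT, and then as better able to detect the true effect.

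The propensity matching does not repair this, because baseline imbalance between the randomised groups triggers it, not completion. What is at stake is how the efficacy estimate is read. The article will compute effect sizes as preliminary evidence, and its Study measures section names the same outcomes for the full-scale trial. Someone planning that trial could take the completers figure to be the cautious one.

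**Working it through.** The article states no effect size, SD, alpha or power, so there is no figure of its own to reproduce. The check asks which way the comparison errs, and by how much.

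**Inputs from the article**
- 30 participants per arm (Participants section).
- Burden of HOLA: 3 walks × 16 weeks = 48 walks.
- Guides to a plausible completion share: the 85% retention criterion and the 80% attendance criterion (section on the feasibility objective). Neither is stated to define completing HOLA.

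**Assumptions**
- Completion share c.
- Correlation r between the propensity to complete and a good outcome.
- Completers are the top share c of a standard normal propensity; the outcome has SD 1.

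**Bias with no true effect**

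The mean propensity among completers is φ(z)/c, where z is the normal quantile at 1 − c. It is 0.274 at c = 0.85, 0.350 at 0.80 and 0.497 at 0.70. The bias is r × φ(z)/c:

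| c | r | Bias toward HOLA (SD) |
|---|---|---|
| 0.85 | 0.3 | 0.3 × 0.274 = 0.08 |
| 0.80 | 0.3 | 0.3 × 0.350 = 0.105 |
| 0.70 | 0.3 | 0.3 × 0.497 = 0.15 |
| 0.70 | 0.5 | 0.5 × 0.497 = 0.25 |
| any | 0 | 0 |
| 0.85 | −0.3 | −0.08 |
| 0.70 | −0.3 | −0.15 |

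A simulation with 30 per arm, a pooled t-test and 40,000 runs per setting agreed to within 0.003 SD for these settings. At r = 0.3, a false result in favour of HOLA occurred in 4.7% (c = 0.85), 5.7% (0.80) and 7.4% (0.70) of runs, against a nominal 2.5%. ITT has no such bias, whatever r is.

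**If there is a real effect**

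Suppose completers gain 0.5 SD and non-completers gain nothing.
- c = 0.85: ITT estimates 0.5 × 0.85 = 0.425. The completers comparison gives 0.50 at r = 0 and 0.50 + 0.08 = 0.58 at r = 0.3.
- c = 0.70: ITT estimates 0.35. The completers comparison gives 0.50 at r = 0 and 0.65 at r = 0.3.

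So in this scenario the completers estimate exceeds ITT even when completion is unrelated to prognosis.

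**Precision**

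The standard error is √(1/30 + 1/30) = 0.258 SD for ITT. With 26 completers (c = 0.85, rounded) it is √(1/30 + 1/26) = 0.268; with 21 (c = 0.70) it is 0.285. The false-positive rates above already include this loss of precision.

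**If the figure were used for planning**

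Sample size varies as 1/effect². Planning on 0.58 when the ITT effect is 0.425 gives (0.425/0.58)² ≈ 0.54 of the required number.

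**The case against.** The strongest defence is about weight. The article says that "this pilot study is not powered to test a hypothesis". Its primary outcomes are feasibility measures, ITT is planned and ranked highest, and the claim about the true effect is hedged with the word may. The tabulated bias at r = 0.3 (0.08 to 0.15 SD) is well below the ITT standard error of 0.258 SD. All of this stands, and it limits the severity. It does not make the label right.

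The direction is also assumed. The severity outcome is change in symptoms, and better health at entry need not mean greater change. Eligibility already requires medical clearance and a walk test, which narrows selection on health. This stands too: the article has no data on the prognosis of completers, so a certain bias toward HOLA cannot be claimed.

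A reader might infer that the completers result could by itself justify a definitive trial. The article does not support that. Its success criteria concern recruitment, refusal, allocation, retention ("Adequate retention will be defined as 85 % or more of randomized subjects completing the post-intervention assessment") and attendance ("Acceptability is defined as 80 % or more of sessions attended by subjects"). None is an efficacy criterion, and nothing ties progression to this comparison.

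A reader might also conclude that a complier-average effect must replace the comparison. Dividing the ITT effect by the share who start the walks assumes that assignment has no effect on non-starters. HOLA's individual session comes before the walks, so non-starters may already have received part of the programme. Controls receive a *fotonovela* and discussion that the plan does not give to the HOLA arm. Both strain the assumption.

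The missing definition of completion is not held against the article, which may leave it to the full protocol or analysis plan.

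**Conclusion.** The description is wrong as written. The comparison is a one-arm completers analysis that breaks randomisation, and neither conservative nor as-treated describes it. It favours HOLA on condition that completers have a better prognosis, by the 0.08 to 0.25 SD tabulated for positive r. Without that link the bias is zero, and with the opposite link it runs against HOLA. Those sizes rest on the assumed r, c and normal model.

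This is a should-fix correction to a supplementary analysis in an unpowered pilot. The feasibility criteria and the ITT analysis are unaffected.

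**What to change.** In the Analysis section:

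1. Delete the description as more conservative, the term as-treated and the reference to a true effect.
2. Label the comparison a supplementary, exploratory completers analysis.
3. Adjust it for baseline symptom severity. This reduces selection on measured severity only; unmeasured health and motivation remain.
4. State that it may favour HOLA.
5. State that effect sizes for planning the full-scale trial come from the ITT analysis.

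A complier-average estimate may be added, but its exclusion restriction must be argued in light of the individual session before the walks and the material given to controls. It also has a wider interval and answers a different question if compliance means starting rather than completing.

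The cost is a few sentences and one covariate per model. Baseline measures are already collected, so no new data are needed.

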## Discussion

Many racial/ethnic minority elderly view traditional mental health services as highly stigmatizing [8, 59, 60]. Since health promotion/health behavior change interventions are culturally relevant [7] and effective in reducing risk factors [24, 29], they may be an optimal prevention strategy in the high-risk racial/ethnic minority elderly. This study will generate evidence of a potentially scalable intervention for depression and anxiety prevention in older Latinos in the midst of a rapid demographic transition. The use of a CHW delivering a health promotion intervention to prevent common mental disorders in Latino elderly is an innovative approach to reduce disease burden in a population living with high exposure to risk factors (comorbid physical and mental health conditions) and disparities in access to and engagement in mental health services [2–6]. Since increased physical activity and pleasant events are each effective in treating geriatric depression and anxiety [25–29], this study will determine whether an intervention that combines these two approaches will be acceptable, feasible, safe, and effective in preventing common mental disorders in older Latinos. By shifting the focus to prevention, and adding a CHW, two physical and social activation sessions, pleasant events scheduling, mood ratings, and pedometers, HOLA is an innovative and self-motivating intervention that makes efficient use of limited resources.

The integrated (mental and physical health) nature of this intervention enhances the innovation and potential clinical impact. In addition, the results of this study could also have implications for other high-risk, highly disadvantaged populations. Older African Americans have low rates of mental health service use [3], experience high stigma [59], and have high rates of co-morbidities [61]. Older Asian Americans also report high stigma [60] and are more likely to express distress through somatic symptoms rather than psychological terms. [62]. All of these groups could potentially benefit from the proposed health promotion intervention in the service of preventing common and disabling mental disorders. The development of a health promotion intervention designed to prevent common mental disorders could be a means of addressing multiple disparities (for example, mental health outcomes, mental health service use, stigma) among racial/ethnic minority elderly people.

### Trial status

Study recruitment, assessment, and intervention delivery activities are ongoing at the time of submission.

## Abbreviations

BA: Behavioral Activation
BAI: Beck Anxiety Inventory
CHW: community health worker
DSM: Diagnostic and Statistical Manual
GAD-2: 2-item Generalized Anxiety Disorder scale
General S-E Scale: General Self-Efficacy Scale
HOLA: Happy Older Latinos are Active
IRB: Internal Review Board
MDD: Major Depressive Disorder
MINI: Mini International Neuropsychiatric Inventory
MMSE: Mini Mental Status Exam
NIH: National Institute of Health
NIMH: National Institute of Mental Health
PCP: primary care physician
PHQ-2: 2 item Patient Health Questionnaire
PI: principal investigator
PR: Public Relations
PSQI: Pittsburgh Sleep Quality Index
QIDS-SR: Quick Inventory of Depressive Symptoms, self-report
RA: research assistant
SLT: Social Learning Theory
T1: Time 1
T2: Time 2
T3: Time 3
T4: Time 4
UM: University of Miami
WHODAS 2.0: World Health Organization Disability Assessment Schedule, version 2.0
